## Abstract

**Background:**

The number of women of childbearing age with Type 2 diabetes(T2DM) is increasing, and they now account for > 50% of pregnancies in women with pre-existing diabetes. Diabetes pregnancies without adequate pre-pregnancy care have higher risk for poor outcomes (miscarriages, birth-defects, stillbirths) and are associated with increased complications (caesarean deliveries, macrosomic babies, neonatal intensive-care admissions). The risks and costs of these pregnancies can be reduced with pregnancy preparation (HbA1c, ≤ 6.5%, 5 mg folic acid and stopping potentially harmful medicines). However, 90% of women with T2DM, most of whom are based in primary care, are not adequately prepared for pregnancy. This study will evaluate a programme of primary care-based interventions (decision-support systems; pre-pregnancy care-pathways; pregnancy-awareness resources; professional training; and performance monitoring) to improve pregnancy preparation in women with T2DM.

**Methods:**

The study aims to optimise the programme interventions and estimate their impact on pregnancy preparation, pre-pregnancy care uptake and pregnancy outcomes. To evaluate this multimodal intervention, we will use a multi-method research design following Complex Adaptive Systems (CAS) theory, refining the interventions iteratively during the study. Thirty GP practices with ≥ 25 women with T2DM of reproductive age (18–45 years) from two South London boroughs will be exposed to the intervention. This will provide > 750 women with an estimated pregnancy incidence of 80–100 to study. The research involves: a clinical audit of processes and outcomes; a process evaluation informing intervention feasibility, implementation, and behaviour change; and a cost-consequences analysis informing future economic evaluation. Performance data will be collected via audits of GP systems, hospital antenatal clinics and pregnancy outcomes. Following CAS theory, we will use repeated measurements to monitor intervention impact on pregnancy preparation markers at 4-monthly intervals over 18-months. We will use performance and feasibility data to optimise intervention effects iteratively. The target performance for the intervention is a 30% increase in the proportion of women meeting pre-pregnancy care criteria.

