### Study setting, sample size and participants

The study will take place in South London where currently a high proportion of women with T2DM become pregnant without effective PPC [3]. We will recruit 30 general practices for intervention exposure. Practices will be considered for inclusion if they have ≥ 25 women with T2DM of reproductive age (18–45 years), this will provide a pooled sample of 750 women. Two local hospital diabetes pregnancy services responsible for the maternity care of 80–100 women with T2DM per year from this area will also participate, so that pregnancy outcomes can be studied.

It is difficult to predict how many women will be actively trying to conceive during the study period (this will be an important finding in itself), but we have estimated based on the number of annual pregnancies reported there will be 120–150 pregnancies in the participating boroughs: with 40–50 pregnancies in the women attending the PREPARED exposed practices. If we assume that women will be trying for pregnancies for 12 months prior to conception, then we can further estimate that > 100 women will be requiring PPC intervention with the remaining women (*n* =  > 650) requiring reproductive review and contraception.

There are high levels of deprivation and ethnic diversity in the local area, hence, establishing intervention reach into these communities is an important objective for the study as these groups of women form a major proportion of the target population.

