### Data collection

The audit data (see Table 1) will be extracted from participating practices using an electronic template that we will install in the participating practices electronic record keeping system, the data collected will identify: women of child bearing age (< 45 years) attending appointments; reproductive assessments (activated on template); glycaemic control; changes to medications or contraception; PPC care-plan initiation; and PPC education or the dispensing of the integrated PREPARED self-help resources (leaflets and web-links). The pregnancy and pregnancy outcome data will be collected from the participating hospital audit systems which routinely collect these data for all women with diabetes as part of an ongoing national audit. The pregnancy booking data includes: glycaemic control; folic acid (5 mg) adherence; the prescription of any teratogenic therapies; and estimated pre-pregnancy weight. The birth outcome data includes: term and status of infant at birth including details of adverse outcomes; mode of birth; breast feeding status; maternal health/injury and depression; pregnancy complications; length of hospital stay; and neonatal care admissions. We will collect these data on all births during the observation period so we can compare outcomes in women from the intervention practices to unexposed practices. The hospital and practice level data will be extracted at baseline (12-month pre-PREPARED exposure) and then monthly to generate run charts monitoring process and outcome performance, with a full audit and review each quarter. The monthly data extractions will be continuous throughout the observation period (18 months). All data will be anonymised at source by hospital/practice administrators, practice codes will allow us to link them to the hospital data.

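### The abstract gives the exposed practices 80–100 pregnancies, twice the 40–50 in the sample-size section, and the counts there carry no stated period

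*Protocol article*

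**What the plan says.** The Methods paragraph of the abstract introduces the thirty practices that will receive the intervention and continues that this will supply more than 750 "women with an estimated pregnancy incidence of 80–100 to study". The sentence refers to those practices, and it gives no period for the count.

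The body section on study setting, sample size and participants gives four figures:

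- 30 practices with at least 25 eligible women each: "this will provide a pooled sample of 750 women".
- Two hospital services "responsible for the maternity care of 80–100 women with T2DM per year from this area". This caseload is not limited to the exposed practices.
- A forecast that "there will be 120–150 pregnancies in the participating boroughs", "with 40–50 pregnancies in the women attending the PREPARED exposed practices". Neither count is given a period.
- A caseload for pre-pregnancy care (PPC): "If we assume that women will be trying for pregnancies for 12 months prior to conception", more than 100 women will need it, leaving more than 650 for reproductive review and contraception.

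The Data collection section sets the observation period at 18 months and plans to collect data on all births in it, so that exposed and unexposed practices can be compared.

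**The concern.** Two different numbers are printed for one quantity, the pregnancies among women in the exposed practices. The abstract's number coincides with the hospitals' yearly area-wide caseload, which suggests that this caseload was attached to the wrong group.

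The count matters because exposed pregnancies form the intervention group for every birth outcome. They are also the women for whom booking data record glycaemic control, folic acid and teratogenic medicines. Study design already confines these measures to the systemic level because they will be rare within a practice, and Data integration and analysis promises a robust estimate of effects. Someone who reads only the abstract would expect twice the exposed pregnancies that the body forecasts.

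The PPC caseload is derived in the same paragraph, apparently from 40–50 pregnancies and 12 months of trying, but the working is not shown.

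**Working it through.** **Inputs.** Abstract: 80–100 pregnancies, exposed practices. Body: 30 practices, at least 25 women each, 80–100 per year at the two hospitals, 120–150 across the boroughs, 40–50 in exposed practices, 12 months of trying. Data collection: 18 months of observation.

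**1. Women.** 30 × 25 = 750. This reproduces.

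**2. Borough count.** 80 × 18/12 = 120 and 100 × 18/12 = 150. Both ends match the printed 120–150 exactly. This is why 18 months is the likeliest period, but it is an inference.

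**3. Exposed count.** 120/3 = 40 and 150/3 = 50. Both ends match the printed 40–50, so on the 18-month reading the body's pregnancy counts agree with each other.

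**4. Abstract against body.** 80/40 = 2.0 and 100/50 = 2.0. The abstract does not reproduce.

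**5. Can another reading reconcile them?**

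- *40–50 is annual.* Over 18 months: 40 × 1.5 = 60 and 50 × 1.5 = 75. The abstract's figure, taken as an 18-month count, is then too high by 80/60 = 100/75 = 1.33. On this reading 120–150 would also be annual, which fits badly with 80–100 per year at the two hospitals.
- *The abstract means every pregnancy studied, exposed or not.* The body's figure for that is 120–150, not 80–100.
- *The abstract's figure is annual and the body's covers 18 months.* The body then gives 40/1.5 = 26.7 to 50/1.5 = 33.3 per year, and the gap widens to three-fold.

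None of these brings the two figures together.

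**6. Precision.** The half-width of a 95% interval around 30% is 1.96 × √(0.3 × 0.7/n), treating pregnancies as the denominator and as independent:

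| Pregnancies | Half-width (points) |
|---|---|
| 40 | ±14.2 |
| 50 | ±12.7 |
| 80 | ±10.0 |
| 100 | ±9.0 |

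**7. PPC caseload.** If each woman tries for 12 months before conceiving, those trying at some time in an 18-month window conceive within 18 + 12 = 30 months. At a constant rate, with 40–50 as an 18-month count: 40 × 30/18 = 67 and 50 × 30/18 = 83. The printed figure is more than 100. Other inputs change the answer:

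- 40–50 taken as annual: 40 × 2.5 = 100 to 50 × 2.5 = 125.
- The 12-month baseline added to the window: 40 × 42/18 = 93 to 50 × 42/18 = 117.
- Women who try without conceiving: about 17 to 33 of them (100 − 83 to 100 − 67) would bring the total to 100.

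**The case against.** The sample-size section, which is the operative text, prints the lower count openly, and no stated calculation uses 80–100. That stands: the error lies in one sentence of the abstract and the design does not depend on it.

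Four stronger readings are tempting, and the documents do not support them.

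- *The whole analysable sample is halved.* It is not. The 750 women reproduce, and the process measures (reproductive review, care pathway, folic acid initiation, contraception) rest on them. The comparison of birth outcomes also uses unexposed births. Only the exposed-pregnancy count is affected.
- *The protocol says that its counts cover 18 months, so the study will certainly have half the pregnancies.* The body states no period. The two-fold ratio is secure as a ratio of printed figures; over 18 months it could be 1.33 if 40–50 were annual.
- *The caseload of more than 100 is wrong and should be 67–83.* The 67–83 counts only women who eventually conceive, at a constant rate. Women who try without success also need PPC, and the protocol says that the number trying is hard to predict. What can be said is that the figure is not reproducible from its stated inputs.
- *Power is lost.* The article states no hypothesis test, alpha or power for these measures; the primary analysis is run charts and percentages followed to a target. A before–after power figure would rest on a test that the reader supplies. Interval width shows the effect without one.

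**Conclusion.** The contradiction is real and is between two printed figures: the abstract gives exposed practices 80–100 pregnancies and the body gives 40–50, a factor of two at both ends. The 18-month reading of the body's counts is a strong inference; on the annual reading the abstract still exceeds the 18-month count of 60–75. With 40–50 pregnancies, the 95% interval around 30% is about ±13–14 points rather than ±9–10. This assumes that pregnancies are the denominator and makes no allowance for clustering by practice. The PPC caseload of more than 100 is a secondary point: its derivation is incomplete, but no error in it is demonstrated.

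**What to change.** 1. Correct the abstract to 40–50 pregnancies in exposed practices, with 120–150 across the boroughs.
2. State the period for every count in the abstract and the sample-size section. If the period is 18 months, say so; if 40–50 is annual, give the 18-month totals and reconcile 120–150 with the hospitals' 80–100 per year.
3. State the precision that goes with the corrected count, about ±13–14 points at 30% for 40–50 pregnancies.
4. For the PPC caseload, state the assumption that produces more than 100 (for example women who try but do not conceive, or annual counts), or restate the figure. The remainder of more than 650 should follow whichever is chosen.

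The cost is a text correction. Design, data collection and analysis are unchanged, but the advertised number of exposed pregnancies becomes less favourable.

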Many of the risks associated with diabetes pregnancies can be ameliorated with improved pregnancy preparation and specific pre-pregnancy care clinic attendance. It is well established that exposure to hyperglycaemia and some treatments prescribed in the management of T2DM can harm the fetus during the period of organogenesis in the first trimester [13, 14]. Unfortunately, many women with T2DM are unaware of these risks [15] and may not realise they have conceived until late into the first trimester of their pregnancy [16]. In response, the National Institute for Health and Care Excellence (NICE) has developed guidelines for pre-pregnancy care (PPC) in women with diabetes which recommends: initiating high-dose (5 mg) folic acid; avoiding teratogenic medications; and intensifying glucose control [17]. However, the uptake of PPC is very low in the UK, with only 10% of women with T2DM meeting the current NICE criteria [3] increasing the risk of adverse pregnancy outcomes [18, 19]. It is also concerning that the majority of these women are from deprived areas and are from Black or Asian minority populations, thereby heightening underlying health inequalities [3]. Hence, establishing effective interventions to improve the uptake of PPC in women with T2DM is a high priority.

Previous prospective cohort studies investigating interventions to improve PPC uptake in women with diabetes have had a limited impact among women with T2DM, increasing uptake by only 7–15% [20–23]. These interventions have included: health professional education; patient information and education on PPC; PPC teams; and clinical guidelines [20–23].

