### Study design

A multimethod design will be used, with a clinical audit of PPC related processes and outcomes; and an integrated process evaluation informing intervention feasibility, implementation, and behaviour change; and an economic cost consequences analysis. The clinical audit will provide PPC performance data. Following CAS theory, we will use frequent repeat measures of the PPC performance metrics to monitor the delivery and impact of the intervention components at four-monthly intervals over 18 months from baseline (performance 12 months pre-intervention). At each timepoint performance measures will be reviewed to inform where intervention effects might need boosting or refining. The target performance for the intervention will be a minimum improvement of 30% at final observation in the proportion of women meeting current NICE pregnancy criteria [17]. Practice level performance will also be monitored considering the number of women: having a reproductive review; accessing PPC; receiving folic acid 5 mg; and instigated on contraception. Table 1 provides an overview of the data that will be used to determine systemic (across the exposed practices) and practice level performance (see Table 1). The PPC and pregnancy outcomes will have a relatively low incidence at the practice level so these will only be considered at the systemic level.

**Table 1 Tab1:** Performance measures

Performance measures	Systemic Performance	Practice Performance
Process data		
• Reproductive review and care plan instigated	Yes	Yes
• Care pathway activation	Yes	Yes
• Initiation of folic acid 5 mg	Yes	Yes
• Contraception advise given	Yes	Yes
• Instigated on contraception	Yes	Yes
• HbA1c testing and results	Yes	Yes
Pre-pregnancy care targets		
• HbA1c ≤ 48 mmol/mol (6.5%)	Yes	No
• Prescription of 5 mg folic acid pre-pregnancy	Yes	No
• Cessation of potentially teratogenic therapies	Yes	No
Pregnancy outcomes		
• Neonatal hypoglycaemia	Yes	No
• Macrosomia (birth weight > 4.5 kg)	Yes	No
• Shoulder dystocia	Yes	No
• Caesarean section incidence	Yes	No
• Neonatal intensive care admissions	Yes	No
• Postnatal length of stay	Yes	No
• Any other adverse outcomes	Yes	No

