### Data integration and analysis

The data will provide ongoing information of intervention performance and implementation. The run charts and emergent findings of the process evaluation will be reviewed monthly with a full quarterly review by the research team and every 6 months by the advisory board to identify areas for refining or boosting intervention components to maximise the programme effects. The target performance for the intervention for the final observation will be achieving a minimum of 30% of women (from intervention exposed practices) achieving the following PPC objectives:HbA1c ≤ 48 mmol/mol (6.5%)Prescription of 5 mg folic acid pre-pregnancyCessation of potentially teratogenic therapies

Practice level performance will also be monitored considering the proportion of women:Having a reproductive review and care plan instigatedEngaged in the pre-pregnancy care pathway—referred to intermediate or hospital diabetes teamsCommencing on folic acid 5 mgInstigated on contraceptionHbA1c testing and results

The extracted data will be imported into SPSS v26 and checked for accuracy (missing data or errors). The primary analysis will be based on collating the collective outcome and performance data from all the participating practices into run charts and performance metrics. In terms of PPC criteria, baseline performance will be established and then we will monitor performance prospectively (four-monthly intervals), to establish progression in performance as percentages to the final 30% target.

Hence, we will be able to provide a robust estimate of intervention effects and costs. We will also be able to compare the antenatal and pregnancy outcome data from the intervention practices to the non-participating practices to establish estimate differences in performance for the main performance measures and pregnancy outcomes. We will also consider practice level variations in process performance.

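### The study's only numerical success target is defined both as a 30% change in a proportion and as an attained level of 30%, and these give different pass marks

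*Protocol article*

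**What the plan says.** The target appears in three sections of the protocol article.

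- **Abstract, Methods:** "The target performance for the intervention is a 30% increase in the proportion of women meeting pre-pregnancy care criteria".
- **Study design:** "a minimum improvement of 30% at final observation in the proportion of women meeting current NICE pregnancy criteria".
- **Data integration and analysis:** "achieving a minimum of 30% of women (from intervention exposed practices) achieving the following PPC objectives". The same section describes the monitoring as intended "to establish progression in performance as percentages to the final 30% target".

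The first two describe a change from baseline. The third describes a level to be reached, and states it twice.

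On the starting point, the Background cites current performance, "with only 10% of women with T2DM meeting the current NICE criteria", and the abstract gives the complement, "90% of women with T2DM, most of whom are based in primary care, are not adequately prepared for pregnancy". Neither is the study's own baseline. That is still to be measured over the 12 months before the intervention: "baseline performance will be established and then we will monitor performance prospectively (four-monthly intervals").

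**The concern.** A change of 30% and a level of 30% are different targets unless the baseline happens to make them equal. The change version is also ambiguous in scale: a 30% increase in a proportion may mean multiplying it by 1.3 or adding 30 percentage points. Two definitions therefore produce three possible pass marks.

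This matters because it is the only numerical success threshold in the article. Under Study outputs and impact, the Discussion makes its main claim, that an implementable programme will be available, conditional on the target being met. If the definition is left open, it can be settled after the run charts have been seen.

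**Working it through.** **Inputs**

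- Target figure: 30% (Abstract; Study design; Data integration and analysis).
- Baseline b: not yet known. The cited background rate of 10% is used as an assumption, with 5% to 20% as a range.
- Possible denominators, from Study setting, sample size and participants: 40 to 50 pregnancies in exposed practices; more than 100 women requiring pre-pregnancy care; 750 women in the pooled sample.

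**The plan's own figures.** The article gives no alpha, power or sample-size formula tied to the 30%, so there is none to reproduce. The pooled sample does reproduce: 30 practices × 25 women = 750.

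**Step 1: final proportion required under each reading**

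Relative change: 1.3 × b. Percentage points: b + 0.30. Attained level: 0.30.

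| Assumed baseline | Relative | Level | Percentage points |
|---|---|---|---|
| 5% | 6.5% | 30% | 35% |
| 10% | 13% | 30% | 40% |
| 15% | 19.5% | 30% | 45% |
| 20% | 26% | 30% | 50% |

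**Step 2: where the readings coincide.** Level and percentage points agree only if b + 0.30 = 0.30, so b = 0%. Level and relative agree only if 1.3 × b = 0.30, so b = 0.30 / 1.3 = 23.1%. Neither is near the cited 10%. From 10%, reaching 30% is a gain of 20 points, or a 200% relative increase (0.30 / 0.10 − 1 = 2.0). It is a 30% change on neither scale.

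**Step 3: the same result judged three ways, at an assumed baseline of 10%**

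| Final result | Relative (13%) | Level (30%) | Points (40%) |
|---|---|---|---|
| 20% | met | not met | not met |
| 35% | met | met | not met |

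Which results are affected depends on the baseline. At 5%, for example, 35% would just meet all three, and 20% would still split them.

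**Step 4: how far chance-of-success figures can be pushed.** Suppose the true rate stays at 10% and the pass mark is 13%. The binomial probability of meeting it without any real change is:

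| Assumed denominator | Count needed | Probability |
|---|---|---|
| 45 (midpoint of 40 to 50 pregnancies) | 0.13 × 45 = 5.85, so 6 | 0.29 |
| 100 (women requiring pre-pregnancy care) | 13 | 0.20 |
| 750 (pooled sample) | 0.13 × 750 = 97.5, so 98 | 0.004 |

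The probability falls by a factor of about 70 (0.292 / 0.0041) across denominators that the article itself offers. These figures illustrate the point and do not support a single error rate. The pass marks in Step 1 need no denominator.

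**The case against.** The strongest reply is that context nearly settles the meaning. The analysis section is the fullest statement: it lists the objectives and gives the level twice. The 13% reading is also hard to believe as an intention. It would mean a gain of 3 points, when the Background calls earlier gains of 7–15% limited and criticises a study that rose from 5.8% to 15.1%. Moreover, the stated aim is to optimise the components and estimate their impact, and percentages will be reported over time, so readers can judge the result whatever it is called.

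Much of this stands. The relative reading is the least plausible, no test or power calculation uses the target, and the percentages will be visible. But discounting the relative reading still leaves 30% against 40% at a 10% baseline. The change wording is also not a slip confined to the abstract, since the Study design section repeats it. Nor can the point be left to a fuller document, because the article states the target inconsistently; it does not merely omit a detail.

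A reader might infer three stronger points that the text does not support:

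- **That there are three separate definitions.** The abstract and Study design say the same thing in nearly the same words. There are two definitions, one of them ambiguous in scale.
- **That the study runs a 29% risk of false success.** That figure needs the least plausible reading, an assumed 10% baseline and the smallest denominator. The target sentences speak of women and do not mention pregnancies.
- **That decisions to boost or refine components depend on the 30%.** Those reviews use performance measures, run charts and process-evaluation findings. Nothing ties them to crossing the threshold.

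**Conclusion.** The inconsistency is real and lies in the current text: a change of 30% in two sections, a level of 30% in a third. With the baseline assumed equal to the cited 10%, the pass mark is 13%, 30% or 40%. Over assumed baselines of 5% to 20%, it is 6.5% to 26%, 30%, or 35% to 50%. Within those ranges the readings never all agree, although the relative mark approaches the level as the baseline nears 23.1%.

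What is affected is whether success can be declared unambiguously, and with it the conditional claim in the Discussion. Power, data collection and the analysis model are untouched. The 10% is a background figure, so 13% and 40% are illustrations that will move once the baseline is observed; the conflict between a change and a level remains.

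**What to change.** Use one definition in the Abstract, Study design, and Data integration and analysis sections. The natural choice is the attained level, at least 30% of women from exposed practices at final observation, because the analysis section already states it twice. Reword the other two sections to match. If the sponsor prefers a change, the text should say whether it is relative or in percentage points, and the analysis section should be reworded instead.

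The sponsor should also name the denominator. The sample-size section offers pregnancies, women requiring pre-pregnancy care, or all eligible women, and the target sentences do not choose among them. That choice is one of substance and should be made explicitly, before the final data are seen.

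Report the observed baseline percentage, the final percentage and the absolute difference alongside the target, so that the result can be read without relying on the label.

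The cost is a wording amendment in the sections concerned plus one decision on the denominator. No new data are needed.
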